### Participant Eligibility

Eligible participants are approached within a hospital setting within 6 weeks of their lung cancer diagnosis. Participants are screened for eligibility by research staff to ensure all inclusion and exclusion criteria are met. For inclusion and exclusion criteria see Table 1. Before randomisation participant eligibility is confirmed within 6 weeks of their diagnosis with histology or cytology, and a formal staging assessment. A full blood count, urea, electrolytes, liver function test, corrected calcium, creatinine and clotting profile will be performed 2 weeks before randomisation. After written informed consent has been obtained a baseline assessment of toxicity and dyspnoea score is taken by research staff and participants must complete the baseline Quality of Life and Hospital Anxiety and Depression Scale (HADS) questionnaires. Participants are then randomised to one of the trial arms.

**Table 1 T1:** Inclusion and exclusion criteria for the FRAGMATIC trial

Inclusion Criteria
Patients meeting the following criteria can be included in the trial:
1. Histopathological or cytological diagnosis of primary bronchial carcinoma (small cell or non-small cell) within the last 6 weeks

2. Age 18 or over

3. ECOG Performance status 0, 1, 2 or 3

4. Willing and able to self-administer LMWH by daily subcutaneous injection or have it administered to them by a carer

5. Willing and able to give informed consent.

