### Sample Size Considerations

This study aims to demonstrate that dalteparin will improve the 1-year survival of lung cancer patients by 5%. Although the median 1-year survival for all lung cancer patients in the UK has been shown to be 20% [1], it is likely that those with a very short life expectancy will not be entered into this study. For this group of patients it is assumed that the 1-year survival in the control group is 25%. To detect an advantage in 1 year survival of 5% with dalteparin (to 30%) a hazard ratio of approximately 0.87, using a 2-sided log rank test with 89% power at a 5% significance level, requires a total of 2047 events (deaths). Accruing 2200 patients (1100 in each group) over 3 years with a further 1 year follow-up should be sufficient to achieve this required number of events [41]. Through discussions with the UK lung cancer clinical community and patient representatives it was deemed that, balancing the additional expense, risk of toxicity and logistics of giving dalteparin, an increase of 5% in 1 year survival was clinically significant. The current rate of VTE ante mortem is 15%, with a post mortem VTE rate in excess of 50% in advanced cancer. The use of thromboprophylaxis could therefore have a larger impact on survival.

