### Outcome Measures

The primary outcome measure is overall survival. Overall survival is calculated from the date of randomisation, to death from any cause. Those patients still alive will be censored at the date last seen.

The secondary outcome measures are: VTE-free survival, metastasis-free survival, toxicity, QoL, dyspnoea, anxiety and depression, cost effectiveness and cost utility.

VTE-free survival will be calculated from the date of randomisation to the date of first clinical evidence of VTE or death from any cause (whichever is the earlier). VTE-free survivors will be censored on the date last known to be alive and free of clinical evidence of a VTE. Metastasis-free survival will be calculated from the date of randomisation to the date of first clinical evidence of metastatic disease or death from any cause (whichever is the earlier) in those patients whose baseline staging indicates no evidence of metastases at the time of randomisation. Metastasis-free survivors will be censored on the date last known to be alive and free of clinical evidence of metastatic disease. Toxicity will be assessed according to NCI Common Terminology Criteria for Adverse Events version 3.0 and any serious adverse events (SAE) are collected in 'real time'. QoL questionnaires will be completed by patients at baseline, 12 weeks, 24 weeks, 9 months and 1 year. QoL will be generally assessed using EQ-5D which includes a core of five domains (mobility, self-care, usual activities, pain/discomfort and anxiety/depression) with three options per domain. A unique EQ-5D health state is defined by combining the scores from each of the 5 dimensions to produce a score from 0 to 1. The impact of dyspnoea (breathlessness) will be assessed using the Cancer Dyspnoea Scale, which consists of twelve items with five options. These items are combined to create three factors that represent the sense of effort, anxiety and discomfort. The impact on mental health (anxiety and depression) will be assessed using the Hospital Anxiety and Depression Scale (HADS), which consists of fourteen items with four options, which are summed to create two subscales 'depression' and 'anxiety'. Cost effectiveness of dalteparin will be assessed. Costs will be monitored prospectively via Case Report Forms (CRF) for 1 year or until death, whichever is soonest. Survival will be adjusted for quality of life using the EQ-5D.

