### Statistical analysis

All analyses will be performed on a full intention-to-treat basis, i.e. all patients randomised will be included, and all patients will be analysed according to their allocated group whatever treatment they received. Descriptive statistics of the patient characteristics within each treatment group will be presented (including a summary of the type of standard anticancer treatment each patient actual received). The main analysis will compare overall survival between the two groups using an unadjusted logrank test. Final analysis will take place when 2047 events (deaths) have been reported, which is expected to be approximately 1 year after accrual closes. Kaplan Meier curves and logrank tests will also be used to compare the two groups on the secondary outcomes of VTE-free survival and metastasis-free survival. N.B. It is possible the data for secondary endpoints (e.g. toxicity) may be mature enough for analysis and presentation before the main overall survival primary endpoint. The secondary outcomes of proportions of patients with toxicities and SAEs such as unexplained death and significant bleeding during the first six months will be compared using a chi-squared test. An assessment of compliance with medication in the dalteparin arm will be made, including an exploration of predictors of poor compliance. Secondary analysis will incorporate an assessment of the impact of compliance on overall VTE-free and metastasis-free survival [42]. The analysis of QoL, dyspnoea, anxiety, and depression endpoints will use both a subject-specific and group based approach. The subject-specific approach will use the data for each individual, the severity of each symptom being plotted against the assessment time and then the areas under the curve (AUC) calculated. The AUC is then standardized by dividing by the number of days between the first and last assessment, resulting in a standardized AUC (SAUC) for each patient, for each symptom. The Mann-Whitney test will be used to compare SAUCs between treatment arms. The group based approach considers the proportion of all patients in each treatment group falling into each symptom category over time. The summary of this data gives an impression of the severity of each symptom at each specific time point in the trial and is compared between treatment arms using a chi squared test. The economic evaluation will be in the form of a cost utility analysis from a secondary care perspective. Mean differential costs between groups will be estimated. Since cost data are often skewed, bootstrapping methods will be used to produce 95% confidence intervals alongside point estimates. Probabilistic sensitivity analyses will account for both parameter and decision uncertainty. The EQ-5D allows estimation of quality adjusted life years (QALYs) which will be the main effectiveness measure in the economic analysis. Between group differences will be estimated using the area under the curve method adjusted for differences at baseline. In the case of non-dominance, results will be reported in the form of an incremental cost effectiveness ratio (ICER) which shows the extra cost of producing one extra QALY. A cost-effectiveness acceptability curve (CEAC) will be used to calculate 95% confidence intervals for the incremental cost effectiveness ratios http://www.euroqol.org. No formal subgroup analyses are planned to look at differences in primary and secondary endpoints between treatment groups within specific groupings based on patient characteristics. However exploratory analysis will be conducted to explore whether there is any consistent benefit from using dalteparin in different subgroups by creating Hazard Ratio plots and carrying out tests for interaction/trend based on chi squared analysis.

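### The QoL, dyspnoea, anxiety and depression SAUCs include the baseline score and are compared without adjusting for it: a valid test that loses precision and shrinks the effect

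*Protocol article*

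**What the plan says.** The Statistical analysis section gives the quality of life, dyspnoea, anxiety and depression endpoints a subject-specific analysis and a group-based one. In the first, an area under the curve is computed for each patient and symptom: "The AUC is then standardized by dividing by the number of days between the first and last assessment". Then: "The Mann-Whitney test will be used to compare SAUCs between treatment arms". No covariate is mentioned.

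Outcome Measures gives the schedule: "QoL questionnaires will be completed by patients at baseline, 12 weeks, 24 weeks, 9 months and 1 year". The first assessment is therefore the baseline. Participant Eligibility makes that score available before randomisation: "participants must complete the baseline Quality of Life and Hospital Anxiety and Depression Scale (HADS) questionnaires", and "a baseline assessment of toxicity and dyspnoea score is taken by research staff".

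Later in the Statistical analysis section, the economic evaluation treats its own area under the EQ-5D curve differently: "Between group differences will be estimated using the area under the curve method adjusted for differences at baseline".

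**The concern.** A score taken before randomisation cannot respond to dalteparin. Here it is averaged into the outcome and then not used as a covariate. Two things follow. The between-arm difference in SAUC is smaller than the difference in the scores measured on treatment, most of all in patients who die early. And between-patient variation that the baseline could explain stays in the error term. At stake are power and interpretability on the patient-reported secondary outcomes of a trial that asks patients to accept 24 weeks of daily injections.

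**Working it through.** **The plan's own figure.** The only stated design calculation is for overall survival. With HR = ln(0.30)/ln(0.25) = 0.8685, two-sided 5% and 89% power, Schoenfeld's formula gives 2043 deaths and Freedman's 2050. At 2047 deaths the power is 89.1%. The stated 2047 reproduces and is untouched by this point. No power or target effect is stated for the SAUCs.

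**Weight of the baseline in the SAUC.** Inputs: visits at 0, 12, 24, 39 and 52 weeks (Outcome Measures, with 9 months taken as 39 weeks), applied to all four endpoints. By the trapezium rule the weight is half the first interval divided by total follow-up, and a constant post-baseline effect keeps 1 minus that weight.

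| Last form | Baseline weight | Effect kept |
|---|---|---|
| Week 12 | 6/12 = 50% | 50% |
| Week 24 | 6/24 = 25% | 75% |
| 9 months | 6/39 = 15.4% | 84.6% |
| 1 year | 6/52 = 11.5% | 88.5% |

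**Average over patients.** Sample Size Considerations states that "it is assumed that the 1-year survival in the control group is 25" per cent. Assume exponential survival, S(t) = 0.25^(t/52), and that survivors complete every form.
- Survival to weeks 12, 24, 39 and 52 is 0.726, 0.527, 0.354 and 0.250.
- Deaths between weeks 12 and 24: 0.726 − 0.527 = 0.199 of all patients, and 0.199/0.726 = 27.4% of those with a post-baseline form. These carry the 50% weight.
- Shares by last form, among patients with a post-baseline form: 0.274, 0.239, 0.143 and 0.344.
- Mean baseline weight: 0.274 × 0.50 + 0.239 × 0.25 + 0.143 × 0.154 + 0.344 × 0.115 = 0.258. At 30% one-year survival it is 0.244.

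A constant effect is therefore reduced by about a quarter.

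**Precision.** Adjusting for a covariate with correlation r multiplies the variance by 1 − r². The article gives no r, so it is assumed.
- r = 0.5: factor 0.75, variance down 25%, equivalent to 1/0.75 = 1.33 times the patients.
- r = 0.7: factor 0.51, variance down 49%, equivalent to 1/0.51 = 1.96 times the patients.

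As a check on that range, suppose every pair of visits has the same correlation, 0.3, 0.5 or 0.7. The baseline-SAUC correlation is then 0.56, 0.71 or 0.84 with follow-up to 1 year, and 0.81, 0.87 or 0.92 with week 12 only. It is high partly because the baseline is inside the SAUC.

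**Simulation.** 800 patients per arm (1100 × 0.726 = 799), 1,500 runs, the mix of last visits above, normal scores, and last visit independent of score. All tests used the same baseline-inclusive SAUC.

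| Between-visit correlation | 0.3 | 0.5 | 0.7 |
|---|---|---|---|
| Type I error, Mann-Whitney | 5.6% | 4.7% | 4.7% |
| Type I error, rank ANCOVA | 5.7% | 5.2% | 5.5% |
| Power at 0.15 SD, Mann-Whitney | 84.1% | 74.5% | 67.8% |
| Power at 0.15 SD, rank ANCOVA | 97.5% | 97.7% | 99.7% |

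The 0.15 SD effect appeared as about 0.11 SD in the SAUC.

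**What adjustment alone does not do.** ANCOVA of the same SAUC sharpens the estimate but leaves it shrunken. So does running change scores through the same trapezium: the weights sum to 1, so the result is SAUC minus baseline, and the arm difference is still (1 − baseline weight) times the effect.

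**The case against.** The case for leaving the plan alone has real force.

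- **Validity.** A rank test on a summary measure is a robust choice for bounded scales, and it keeps its type I error. A reader might infer that chance baseline imbalance biases the comparison. It does not: such imbalance is already part of the test's null distribution, and at 800 per arm the standard error of a baseline difference is only √(2/800) = 0.05 SD. This stands.
- **Consequence.** These are secondary endpoints with no stated power. Scaling the simulated Mann-Whitney power from 0.15 to 0.20 SD gives roughly 98%, 94% and 90%, so the loss matters mainly for small effects. This stands.
- **Shrinkage.** It is measured against an effect already at full size by the first post-baseline visit. If the effect builds in a straight line from randomisation to week 12, the SAUC is a fair time average over the whole period. This stands as a limit on interpretation, though not on the loss of precision.
- **The QALY analysis.** A reader might infer that the article contradicts itself by adjusting one EQ-5D area for baseline and not the other. It does not. QALYs combine survival with utility and feed a cost ratio that needs a mean difference, whereas the SAUC is a time-averaged score. Only EQ-5D is shared. It is an unexplained difference in method.
- **The group-based analysis.** It compares symptom categories at each time point, so the baseline is not averaged in. It is also unadjusted, so it does not recover the lost precision.
- **The unseen analysis plan.** It could add an adjusted analysis. But the article names the test, so the point concerns a stated choice.
- **Baseline dyspnoea.** The article does not say that the score taken by research staff is the Cancer Dyspnoea Scale. For that endpoint a matching baseline is likely but not certain.

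**Conclusion.** The point holds as a loss of efficiency on secondary endpoints. The planned test is valid and the 2047-death design is unaffected.

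The baseline weights, from 50% down to 11.5%, follow from the visit schedule and the trapezium rule. The average shrinkage of about a quarter also needs exponential survival with 25% alive at 1 year, forms completed by all survivors, and an effect that is constant after baseline. The 25% to 49% fall in variance rests on an assumed baseline-SAUC correlation of 0.5 to 0.7, for which the article gives no value. Since the baseline is already collected and the same section already adjusts for it in the QALY analysis, the improvement is close to free and worth making.

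**What to change.** - Compute each SAUC from post-baseline scores only, or from post-baseline changes from baseline, leaving the baseline point itself out of the average. A patient with a single post-baseline form contributes that score.
- Compare arms by ANCOVA with the baseline score as covariate, or by rank ANCOVA or a proportional-odds model if the scores are skewed.
- Report the adjusted difference with its 95% confidence interval.
- Keep the unadjusted Mann-Whitney test as a sensitivity analysis.
- State that the baseline dyspnoea score is taken with the same scale as the later ones, if that is so.

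The cost is a few sentences in the analysis plan. It needs no new data, patients or visits, and it brings these endpoints into line with the baseline adjustment already planned for QALYs.

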
## Discussion

This Cancer Research UK funded trial will be one of the biggest lung cancer trials ever conducted in the world and will be the first to determine whether the addition of LMWH to routine treatment will be advantages in terms of overall survival in patients with lung cancer.
